#### Staggered and split and social assistance disbursement (staggered and split)

Participants in the ‘staggered and split’ intervention study arm have their social assistance payments released twice a month on days that do not fall during the week of government cheque issue. The days of income assistance receipt are spaced 2 weeks apart and determined at random. As with the staggered intervention arm, individual cheque issue days are established in relation to government cheque issue day and participants transition to their new schedule incrementally. The first individual cheque issue day falls in the week following government cheque issue, with the second occurring on the corresponding day of the week 2 weeks later. This could be, for example, Tuesday of the week following government cheque issue day and Tuesday 2 weeks after that day. This allows for five randomization possibilities for the staggered and split intervention study arm. Participants are again provided with a schedule of their individual cheque issue days for the duration of their study participation.

The change in social assistance payment schedules for both intervention arms is managed through Pigeon Park Savings, which has developed a system, in conjunction with standard social assistance direct deposit services from the British Columbia Ministry of Social Development and Social Innovation, that varies when individuals have access to their social assistance payments. Social assistance payments are directly deposited into the participant’s account, and the system “locks” their payment so that these funds cannot be withdrawn. Money is “unlocked” according to the participant’s disbursement schedule that determines both the timing and frequency at which payments are released. Intervention arm participants can develop personalized arrangements that ensure access to essential funds at specific times to prevent housing instability or payment default. A study liaison at Pigeon Park Savings manages account creation, direct deposit requests to the Ministry and the implementation of holds and releases of funds. Accounts include unlimited withdrawals and a bank card with no-fee withdrawals at credit union automated teller machines. Pigeon Park Savings banking fees are charged at a rate of $5/month, and individuals are not required to pay this fee while they are enrolled in the study.

### Follow-up assessments

Once individuals enrol (control arm) or receive their first payment on their individual schedule (staggered and staggered and split) arms, follow-up visits occur every 2 weeks for the 26-week period of active study participation, for a total of one baseline and 13 regular follow-up interviews. Frequent follow-up visits mitigate recall-related threats to data reliability for key measures [38]. During study follow-up visits, a trained interviewer administers the follow-up questionnaire, which includes past 2 week assessments of all study measures. Participant safety, including the monitoring of adverse events or serious adverse events related and unrelated to study participation is also assessed at every follow-up. Follow-up visits take 20–30 min. Due to the intent-to-treat nature of the study, participants can withdraw from the intervention but are encouraged to continue to complete regular follow-up visits.

### Qualitative parallel process evaluation

The TASA study also includes a qualitative parallel process evaluation concurrent to the quantitative survey-based evaluation of the study interventions. This evaluation is comprised of a longitudinal, nested study involving a sub-population of TASA study participants who complete three qualitative interviews each, the first at baseline, the second at their study mid-point and the third at study completion or withdrawal. Following randomization to the study interventions, approximately 45–50 participants are selected to be participants in a qualitative parallel process evaluation. Quota sampling ensures heterogeneity across categories of social assistance, drug use practices and study arms, with a weighted distribution focusing on the experiences of individuals allocated to the intervention arms (8–10 participants recruited from control versus 15–20 from each intervention arm). Following a separate informed consent process specific to qualitative participants, audio-recorded interviews are conducted by trained qualitative interviewers in private settings at the study site. Data collection follows principles of data saturation in which the study team continues to recruit participants until no new themes emerge in relation to key topics from interviews among individuals in each of the study arms [39, 40]. Interviews employ topic guides informed by previous studies conducted by the investigative team [5, 6, 41] and a comprehensive review of the relevant literature. Baseline interviews explore prior experiences of social assistance receipt, income and material hardship, substance use patterns, and financial management. Midpoint interviews focus on transitions to new payment schedules as well as changes in material circumstances, financial management, drug use patterns and expenditure on drugs. Exit interviews explore study experiences of social assistance receipt and broader changes to life circumstances (e.g. income, housing), drug use and drug-related activity, and reasons for study or intervention withdrawal, where applicable. Initial interviews inform subsequent interviews among the same participants, building on previous responses and benefits or challenges previously identified by participants.

### Study completion and post-evaluation questionnaires

At the final regular follow-up study visit, participants are administered a study completion questionnaire that assesses, in addition to regular follow-up measures, their participation experiences and opinions about the intervention. Sixty days post study completion, a follow-up interview is administered to assess the safety of participants and any significant changes following the completion of the study protocol. Participants in all study arms are able to access the study intervention of their choice following the completion of their participation should they wish to do so. Screening, baseline, follow-up, qualitative and post-evaluation study visits take place at a purpose-built field research office located in the DTES and operated by the British Columbia Centre for Excellence in HIV/AIDS. If needed, follow-up visits can take place at the participant’s residence, over the phone, or other space considered safe by the participant.

### Participant honoraria

Consistent with standard practice in research involving PWUD [34, 42], participants are compensated for their time and interview-related expenses with honoraria in the following Canadian dollar (CAD) amounts: $30 for baseline/randomization visit; $10 per follow-up interview, with follow-up interview incentive bonuses following the first post-baseline follow-up ($10), the completion of five follow-up interviews ($15), the completion of nine follow-up interviews ($20) and the completion of the final follow-up interview ($25). The post study follow-up interview honorarium is $15. The honorarium for each qualitative interview is $30 per interview. Participants will therefore receive a maximum of $245 for participation in the quantitative portion of the study and $335 for participation in both the qualitative and quantitative study components.

### Measures

Table 1 outlines the measures taken at screening, baseline, follow-up, withdrawal and study exit interviews and through post-study data linkages. For all primary and secondary outcomes of interest described below, we collect data on indicators on government cheque issue days by tracking activity and exposures on a daily basis or through specific questionnaire items and response options. Where government cheque issue and individual cheque issue timing are not the same (i.e., for intervention participants), we additionally ask specific questions about individual cheque issue day activities and exposures. By collecting information about the occurrence of key outcomes of interest on non-cheque issue days as well as those coinciding with government and individual payments, we are better able to distinguish between individual cues for increased drug use coinciding with individual payments and social cues prompted by synchronized payment across the population on government cheque issue day.

#### Socio-demographic information and housing status

Socio-demographic information, collected at baseline, includes standardized measures of age, gender, ethnicity, relationship status and highest level of educational attainment. Self-reported measures of residency and housing status include neighbourhood of residence, type of residence (e.g. house, apartment, single room occupancy hotel [43], no fixed address), and housing stability, measured by the number of residences occupied in the last six months (baseline) or past 2 weeks (baseline and follow-up).

#### Drug use (timeline follow back; primary outcome measure)

The TASA study’s primary outcome is increased intensity of drug use on government cheque issue day (i.e. a binary outcome). Participant drug use is considered to have intensified if, in the 3 days starting with government cheque issue day, a participant increases by 40 %: (1) the daily frequency of non-cannabis drug use; (2) the street value of drugs consumed; or (3) the number of non-cannabis substances used, including alcohol and illicit prescription opioids, all compared to the average frequency, value of drugs used or number of substances used on all other days of the calendar month. For example, if an individual uses crack cocaine once daily on non-cheque issue days and does not use methamphetamine, but increases uses crack cocaine 3 times per day and methamphetamine once per day on the 3 days beginning with cheque issue day, they will have intensified their use according to the first and second criteria. These cut points were selected based on prior empirical studies [8] and our intention to capture changes among high-intensity users that could be overlooked if more blunt measures common to RCTs among PWUD, such as daily drug use [44], are used. Staff gather data measuring the primary outcome using the Timeline Follow Back (TLFB) instrument, a reliable, validated, calendric instrument that collects daily information on drug use patterns, including drugs used and frequency of use [30, 31]. We additionally collect participant estimates of the street value of drugs used as a proxy for quantity or dosage of drug consumed, which may not be captured by drug use frequency measures [45, 46]. We also use daily TLFB drug use data to assess our key secondary outcome of intensified drug use on individual cheque issue days, identified using the same frequency, street value or number of drugs criteria as intensified drug use on government cheque issue day.

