There are potentially important differences between the two interventions that may affect their relative efficacy. For example, staggering social assistance payments could displace consumption for individuals away from government cheque issue, but may not reduce overall consumption. At scale, this may improve experiences of service providers who would not have to manage cyclical escalations in service demand, but may provide little benefit to individual PWUD other than improved service access. Staggering and splitting income assistance payments may support smoothing consumption patterns, but may potentially result in multiple periods of escalated drug use signaled by more than one monthly payment. The testing of two different payment schedules enables us to examine which approach, if either, more effectively decreases spikes in drug use and drug-related harm coinciding with synchronized social assistance disbursement.

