### Interventions

#### Control group

Participants randomized to this study arm receive no intervention. They continue to receive monthly social assistance payments according to the British Columbia Ministry of Social Development and Social Innovation disbursement schedule.

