#### Staggered social assistance disbursement (staggered

Participants in the ‘staggered’ intervention study arm have access to their social assistance payments on a monthly basis on a day that does not fall during government cheque issue week and that is not the same as all other participants in the staggered arm. Due to the variation in government cheque issue day timing, which ranges from the 16^th^ to the 29^th^ of the month, individual cheque issue is allocated relative to government cheque issue day (e.g., Tuesday the week after cheque issue). Participants undergo a transition period during which they receive their social assistance up to 7 days later each month until they reach their study cheque issue date. This transition period ensures that participants do not have a time period between payments any longer than the longest period between payments on the government schedule, which is 35 days. To facilitate timely transitions to the new disbursement schedule within the timeframe of the intervention, possibilities for individual cheque issue is are limited to business days during the first and second week following government cheque issue day. This allows for 10 possible payment schedules for participants in the staggered arm. The exact date of disbursement is determined at random through a second randomization procedure. Study staff provide each participant with a detailed payment schedule to assist participant recall.

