### Participant safety

The design of the current trial does not involve any change in the amount of social assistance provided to participants, and we therefore do not anticipate any negative changes to their financial well-being. However, desynchronizing social assistance may disrupt money management strategies, potentially interfering with the payment of expenses. Importantly, most participants in the TASA study have the rent portion of their social assistance paid directly to their landlords. Participants who have rent or other expenses can make arrangements on a case-by-case basis with Pigeon Park Savings to ensure the availability of funds at the appropriate time. Additionally, for staggered and split arm participants, receiving multiple payments per month may result in more frequent periods of intensified drug use, albeit these periods will likely be shorter or less intense given that less money will be disbursed at any one time. For intervention participants, there may also be challenges transitioning onto or off of a new social assistance payment schedule at the start or end of the study period. To mitigate this concern, study staff members can provide referrals to financial management support services as appropriate. We do not anticipate the study will expose participants to unusual risks. Nevertheless, we monitor participant safety as a part of each bi-weekly participant assessment, including considerations of food and housing insecurity, exposure to violence, access to critical health and social services and other emerging issues. We follow standard reporting procedures for adverse events and serious adverse events [64], including oversight from an external, independent Data Safety and Monitoring Committee (DSMC). Participants are able to withdraw from the intervention, the study, or both at any point, and may be withdrawn from either by investigators in the event of concerns over safety.

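### The primary outcome's comparison days include the intervention participants' own paydays, so any rise in use on those days lifts the 40% threshold in the intervention arms only

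*Protocol article*

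**What the plan says.** All references are to the protocol article.

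- **Outcome (Measures, Drug use).** Use has intensified if, "in the 3 days starting with government cheque issue day, a participant increases by 40" per cent on any one of daily frequency, street value or number of substances, "all compared to the average frequency, value of drugs used or number of substances used on all other days of the calendar month".
- **Control group.** "They continue to receive monthly social assistance payments according to the British Columbia Ministry of Social Development and Social Innovation disbursement schedule".
- **Staggered arm.** One payday per month, "limited to business days during the first and second week following government cheque issue day".
- **Staggered and split arm.** Payments are "released twice a month on days that do not fall during the week of government cheque issue".
- **Expected behaviour.** The Background says that "staggering social assistance payments could displace consumption for individuals away from government cheque issue, but may not reduce overall consumption". Participant safety says that in the split arm "receiving multiple payments per month may result in more frequent periods of intensified drug use", but expects each such period to be briefer or milder because less money is released at a time.
- **Hints of a narrower reference.** The worked example under Drug use takes days without cheque issue as its baseline. The opening of Measures treats non-payment days, government cheque days and individual paydays as three kinds of day, in order to separate individual from social cues.
- **Related secondary outcomes (Study design; Drug use).** These include overall monthly drug use, and intensified use on individual cheque days by the same three criteria. The comparison days for the latter are not spelled out.

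**The concern.** The primary outcome is a ratio, and randomisation changes what goes into its denominator. In the control arm the payday lies in the numerator window. In the intervention arms the individual paydays lie among the comparison days. If use rises around those paydays, which the protocol itself foresees, the comparison average rises and so does the level of government-day use needed to count as intensified. A participant whose use on government cheque days is unchanged can then move from positive to negative because of heavier use on another day.

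What is at stake is the interpretation of both comparisons with control: the outcome as written cannot separate a smaller government-day peak from a higher comparison level. The covariates listed under Quantitative analyses do not remove this, because it arises when the outcome is derived.

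**Working it through.** **1. The planned difference, for scale.** Inputs from Sample size: control rate 85%, difference 20%, 80% power, 5% significance (two-sided assumed), 6 repeated measures, correlation 0.6.
- Read as relative (85% v 68%): 97 per arm for a single measure; 97 × (1 + 5 × 0.6)/6 = 64.7, so 65, the stated number of completers. With 33% of observations missing (about 4 of 6 left): 97 × (1 + 3 × 0.6)/4 = 67.9, so 68; 68/0.75 = 90.7, so 91 per arm, as stated.
- Read as absolute (85% v 65%): 73 × 0.667 = 48.7, so 49, which is not the stated figure.

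The planned difference is therefore 17 points on the relative reading, which reproduces the sample size, or 20 points on the absolute one.

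**2. Threshold on government cheque days.** Assume a 30-day month (27 comparison days), ordinary use = 1, and own-payday use = k for 3 days per payment. The document does not give k. I take k = 3, the rise in crack use in the protocol's own example, with 2 and 4 as a range.
- Control: 1.4 × 27/27 = 1.40.
- Staggered: 1.4 × (24 + 3k)/27.
- Split, full excess at each payment: 1.4 × (21 + 6k)/27.
- Split, half the excess at each payment: 1.4 × [21 + 6(1 + (k − 1)/2)]/27, which equals the staggered value.

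| k | Control | Staggered | Split, half excess | Split, full excess |
|---|---|---|---|---|
| 2 | 1.40 | 1.56 | 1.56 | 1.71 |
| 3 | 1.40 | 1.71 | 1.71 | 2.02 |
| 4 | 1.40 | 1.87 | 1.87 | 2.33 |

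Example: government-day use of 1.5 with k = 3 gives 1.5/1.00 = 1.50 (intensified) against the control denominator, and 1.5/1.222 = 1.23 (not intensified) against the staggered one.

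**3. Effect on the rate.** Assume that the payday multiple g is log-normal with median 2 and 85% at or above 1.4, so the log SD is ln(2/1.4)/1.036 = 0.344. Write x = g − 1.

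*Government-day use unchanged, same multiple on own paydays.*
- Staggered: 1 + x ≥ 1.4(1 + x/9), so g ≥ 1.474, and the rate is 81%.
- Split, full excess: 1 + x ≥ 1.4(1 + 2x/9), so g ≥ 1.581, and the rate is 75%.
- Split, half excess: as staggered, 81%.

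The rate against ordinary days is 85% throughout.

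*Half the excess leaves government days for the own paydays, total use conserved.*
- Against ordinary days: 1 + x/2 ≥ 1.4, so g ≥ 1.80, and the rate is 62%.
- As defined: 1 + x/2 ≥ 1.4(1 + x/18), so g ≥ 1.947, and the rate is about 53%. This holds in both intervention arms, because the same total excess is moved.

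**4. Sensitivity.** With government-day use unchanged and the median varied from 1.75 to 3.0, the staggered rate is 79-83% if each person's own-payday spike equals the government-day spike. It is 38-81% if own-payday use is fixed at 2 to 4. The artefact thus ranges from about 2 to 47 points.

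**The case against.** **A relative peak may be what is meant.** The trial aims at spikes relative to the rest of the month and at smoother consumption. A participant whose government days no longer stand out has been desynchronised, and displacement might count as success. This is a fair reading of the motivation. However, the stated objective is to reduce use in the days around cheque issue, and the text does not say that a higher level elsewhere in the month should count as benefit.

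**The secondary outcomes would show displacement.** Overall monthly use and individual-payday use are pre-specified, and daily data are collected. They would help a reader interpret the primary result, but they do not correct it.

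**The wording may intend the exclusion.** The worked example's baseline suggests so. The operative definition does not say it, and the two should be reconciled.

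**The large figures need extra consumption.** The amount of assistance is unchanged. At a multiple of 2, leaving government-day use untouched and adding full spikes raises monthly use from 27 + 6 = 33 units to 36 (staggered) or 39 (split). Other income could fund this, but the conserved case is at least as plausible and gives about 9 points. This stands as a limit on size.

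**Three criteria, not one.** The outcome is positive if any criterion is met, so a participant changes status only if all three fall below their raised thresholds. The single-ratio model ignores this. This also stands.

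A reader might infer that the split arm is favoured most, since it has two paydays among the comparison days. That requires more total excess over the two payments than over one full payment; the protocol expects weaker spikes, and at half the excess each the two arms are equal. A reader might also infer that the individual-cheque-day outcome has the mirror fault. That holds only if the same comparison days apply, which the text implies but does not state.

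**Conclusion.** The point holds. As written, the reference level depends on the randomised arm, and any rise in use around an own payday raises the 40% threshold in the intervention arms only. The bias is towards the interventions. That direction needs only the definition, the payment schedules and some own-payday rise.

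The size is not determinable from the document, which gives neither the spike nor its spread. The conserved-use illustration (about 9 points) and the unchanged-use illustration (4 points in staggered, 4 to 10 in split) are material beside a planned 17 or 20 points, but they rest on an assumed log-normal, a single criterion and a 30-day month. Because government cheque day ranges from the 16th to the 29th, a calendar month will usually hold one staggered payday but at times none or two, so the effect varies by cycle.

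The documents do not support saying that the whole planned effect could be artefact, that the split arm is favoured most, or that the secondary outcome is certainly affected. The sample size is not affected, because it takes only outcome rates as inputs.

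**What to change.** Under Drug use (primary outcome measure), define the reference days in every arm as days of the month outside both the 3 days from government cheque day and the 3 days from each payment actually released to the participant. Tying the exclusion to actual release means that participants who withdraw from the intervention and return to the government schedule, but stay in the intention-to-treat analysis, have no extra days excluded. State also whether personalised early releases for essential expenses count as payments for this purpose.

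Use the same reference days for the individual-cheque-day outcome and say so. Keep the all-other-days version as a sensitivity analysis. This agrees with the three kinds of day set out at the start of Measures and with the worked example.

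With own-payday windows removed, the denominator in the illustration is 1.00 and the threshold 1.40 in all three arms. The cost is wording and derivation code, since daily Timeline Followback data and payment schedules are already held. The downside is about 3 (staggered) to 6 (split) fewer comparison days per month, so a slightly noisier reference average in those arms.

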Drug-related concerns coinciding with cheque issue may be particularly acute in inner-city neighbourhoods with higher prevalence of illicit drug use and concentrations of social assistance recipients [26]. The Downtown Eastside (DTES) neighbourhood in Vancouver, Canada is one such area, commonly characterized by: high rates of poverty; an open drug market; high prevalence of illicit drug use, mental health disorders, and HIV infection; and a large proportion of residents receiving government assistance [27]. Cheque issue days, generally on the last Wednesday of each month, are referred to locally as “Cheque Day” or “Welfare Wednesday”. The widespread and severe harms produced by synchronized social assistance are widely acknowledged among community members and service providers and have been documented by over 20 years of ongoing observational research [7, 24, 28]. The identification of public health- and community safety-promoting approaches to the disbursement of social assistance is therefore an urgent public health and community safety priority in Vancouver as elsewhere, with significant implications for policy and service provision.

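### For the key secondary outcome (intensified use on individual cheque issue days), the arm comparison is confounded by day of week, with unknown direction and size, and nothing in the stated analysis removes it

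*Protocol article*

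**What the plan says.** All references are to the protocol article.

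- **Outcome.** The Measures section on drug use (Timeline Followback, TLFB) states: "We also use daily TLFB drug use data to assess our key secondary outcome of intensified drug use on individual cheque issue days". It uses the same frequency, street-value and number-of-drugs criteria as the primary outcome. There, the 3 days from the government cheque day must show a 40% increase "compared to the average frequency, value of drugs used or number of substances used on all other days of the calendar month".
- **Control paydays.** Under Control group: "They continue to receive monthly social assistance payments according to the British Columbia Ministry of Social Development and Social Innovation disbursement schedule". The Background places government cheque days "generally on the last Wednesday of each month".
- **Staggered arm.** Paydays are random among "business days during the first and second week following government cheque issue day", which gives 10 possible schedules.
- **Split arm.** The first payday is in the week after government cheque issue, "with the second occurring on the corresponding day of the week 2 weeks later", which gives five possible schedules.
- **Analysis.** The Quantitative analyses section contrasts arms by indicator variables. It adjusts for type of assistance, change of financial provider, socio-demographic characteristics with treatment enrolment and neighbourhood, and days from government cheque issue to the study visit. The last is there for recall. None is a weekday or weekend term.

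**The concern.** Weekday is tied to arm by design. Randomising paydays within the intervention arms does not balance it, because controls are never spread over the week. The score divides use in a 3-day window by use on a comparator that mixes weekdays and weekends. Any weekly rhythm in drug or alcohol use therefore enters the score differently by arm.

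This outcome carries real weight. The Background accepts that staggering might only displace consumption and that splitting might create several periods of heavier use. The individual-payday outcome is the one that tests this, and the article calls it key. If its contrast mixes payday response with weekday, a displaced spike could be overstated, understated or hidden.

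**Working it through.** **1. Schedule counts.** 5 business days × 2 weeks = 10 staggered schedules, and 5 × 1 = 5 split schedules. Both match the article and confirm that start days run Monday to Friday.

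**2. High-use days in each 3-day window.** Equal allocation over weekdays is assumed.

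| Assumed high-use days | Mon | Tue | Wed | Thu | Fri | Intervention mean | Control (Wed) |
|---|---|---|---|---|---|---|---|
| Sat–Sun | 0 | 0 | 0 | 1 | 2 | 0.6 | 0 |
| Fri–Sat | 0 | 0 | 1 | 2 | 2 | 1.0 | 1 |
| Fri–Sun | 0 | 0 | 1 | 2 | 3 | 1.2 | 1 |

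**3. Effect on the ratio with no payday response at all.** Take a 28-day cycle with use on high days multiplied by W = 1.25. Ratio = window mean ÷ mean of the other 25 days.

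Sat–Sun rise:
- Mon, Tue or Wed start: 1 ÷ [(17 + 8 × 1.25)/25] = 1 ÷ 1.08 = 0.926
- Thu start: (3.25/3) ÷ [(18 + 7 × 1.25)/25] = 1.083 ÷ 1.07 = 1.012
- Fri start: (3.5/3) ÷ [(19 + 6 × 1.25)/25] = 1.167 ÷ 1.06 = 1.101
- Intervention mean: (3 × 0.926 + 1.012 + 1.101)/5 = 0.978, against 0.926 in controls

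The same calculation gives 1.013 v 1.012 for a Fri–Sat rise and 0.994 v 0.976 for a Fri–Sun rise. With W = 1 every ratio is 1.

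**4. Effect on the scored proportion, staggered arm minus control.** Assumptions: Poisson use of 3 or 6 per day, the same payday rise (×1.4 to ×1.6) in every arm, and the frequency criterion only. The true difference is zero.

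- Sat–Sun rise of 25–50%: about +6 to +18 points
- Fri–Sat rise: about 0 to −6 points
- No weekly pattern: zero

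**5. Sensitivity to the base rate.** Step 4 gives control rates below 85%, the article's only control figure (Sample size section, given for the primary outcome). A second model fixes the base at 85% and lets the payday rise vary lognormally (log-SD 0.3 or 0.6, assumed). For high-day rises of 10–50% it gives +0.8 to +8.0 points for Sat–Sun, −0.1 to −3.3 for Fri–Sat and +0.3 to −2.3 for Fri–Sun.

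**6. Split arm.** The other payday window lies among the other days of the month. With no weekly pattern and a payday rise of ×1.6, the comparator is (22 + 3 × 1.6)/25 = 1.072. The ratio falls from 1.6 to 1.6/1.072 = 1.49. At ×1.4 it falls to 1.4/1.048 = 1.34, below the 40% threshold. Under the step 4 assumptions the scored rate is about 6–12 points below control with no weekday effect. A Sat–Sun rise of 25% brings the net difference to about −3 to +1.5 points, so the net bias can have either sign.

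**The case against.** The documents say nothing about weekend drug use, so any bias is conditional. With no weekly pattern the weekday part vanishes. The Background's wording on Wednesdays allows exceptions. The 3-day window for individual paydays is implied by the shared criteria, not restated. The trial describes itself as exploratory, only a secondary outcome is affected, and a full protocol or analysis plan may handle weekday. The simulations use one of three alternative criteria, and at an 85% base rate the figures shrink. All of this stands. It limits what can be said about size but leaves the imbalance in place: the article itself fixes the paydays, the comparator and a list of adjusters, and together these tie weekday to arm.

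A reader might infer that weekend use makes both interventions look worse. The documents do not support that. It follows for the staggered arm only if the high-use days are Saturday and Sunday. A Friday–Saturday rise gives equal mean exposure and can favour the interventions, and a Friday–Sunday rise gives small effects of either sign. In the split arm the other payday pulls the other way.

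A reader might also infer that simple weekday matching cures the problem. It does not for the split arm, because the second payday falls on the same weekday two weeks later. Its 3 days then make up 3 of about 9 comparator days. At ×1.6 the ratio becomes 1.6 ÷ [(6 + 4.8)/9] = 1.33, and simulation gives a spurious gap of about −14 to −32 points.

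**Conclusion.** The point holds as a design-induced confounding of arm with day of week in a key secondary outcome. The imbalance (0.6 v 0 Saturday or Sunday days per window) follows from the article, given equal allocation and Wednesday government paydays. The bias depends on a weekly use pattern that the documents do not give. The figures above therefore show what is possible under stated assumptions and do not estimate what will occur. The split arm has a second, separate distortion from its other payday, which needs no weekly pattern. The primary outcome is free of this weekday imbalance, because every arm is scored on the same government window. Because the sign is unknown, the result could not be corrected by argument afterwards, so the definition is worth settling before analysis.

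**What to change.** For the individual-payday outcome only, compare each 3-day window with the same three weekdays in the participant's non-payday weeks, and exclude the split arm's other payday window from the comparator. In simulation this held the spurious difference within about 2 points in both intervention arms. Alternatively, model the daily TLFB data with day-of-week terms and an indicator for every payday window.

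Either change needs a sentence in the outcome definition and a little programming on daily data already collected. It changes no visit, payment or randomisation procedure. The cost of matching is a smaller comparator, about 9 days with monthly payment and 6 in the split arm, and so slightly noisier scoring.
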